## 4. Translational Aspect—GRAY-ZONE

The current literature shows that in patients presenting with chest pain, high-sensitive troponin levels above the 99th percentile are indicative for future cardiovascular events, even when acute coronary syndrome was ruled out. Most of these non-ACS-patients are discharged without specific/ preventive therapy (anti-platelet or anti-lipid), although ‘positive’ troponin values (any value at any time during hospitalization above the 99th percentile) seem to clearly indicate underlying myocardial ischemia. In summary, there is an unmet need with a huge potential to reduce mortality and morbidity in ER patients by specific therapy. GRAY-ZONE is an ongoing clinical trial, fully financed by the German Research Foundation, and initiated by the German partner. A total of 3000 troponin positive patients presenting at ER/ CPU with acute chest pain, but ruled-out ACS, will be assigned randomly to Aspirin and/ or Atorvastatin versus placebo (2 × 2 factorial design). The primary endpoint is a composite of non-fatal stroke, non-fatal MI and cardiovascular death. The final biomarker signature, which will be derived within the PREMED-CAD project will be translated and validated retrospectively in GRAY-ZONE. Therefore, we will be able to assess whether this signature is capable of predicting those subjects developing a clinical ischemic event during the 12-months follow-up. Bio-banking in the GRAY-ZONE trial is available at baseline and at 12-months follow-up. This will allow us to investigate the dynamics within the identified biomarkers and final biomarker signature; and also in the clinical event rate in PREMED-CAD-biomarker positive versus PREMED-CAD-biomarker negative patients of the three active, well-tolerated therapies (Aspirin, Atorvastatin, Aspirin combined with Atorvastatin). This project directly paves the way to personalized and biomarker-guided therapy.

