## 5. Challenges and Risks

Because of the complexity of the project including the translational approach, this project has explicit challenges and risks. The project is based on the ‘stratification tool’—the biomarker signature—which allows the identification of subjects at early risk for myocardial infarction. The translational quality of the biomarker signature will be evaluated by the application in the randomized GRAY-ZONE clinical trial. This will allow, by immediate post-hoc analyses, to determine the diagnostic value of the biomarker signature (‘at risk’ = MI within 12 months). Moreover, the exclusive access to this clinical trial allows the therapeutic evaluation of the biomarker signature, since the ischemic subjects of the clinical trial will be assigned to four different medication therapies. This implies that the early stage of biomarker derivation is crucial for all following steps. There is no immediate clinical endpoint in our trial—a weak and insufficient signature will endanger all following steps and the translation into the clinical trial. On the other hand, this collaboration bears the potential to carry a biomarker signature from early development up to ultimate diagnostic application in an ongoing clinical trial, and even towards personalised medicine application using therapy-response analyses. Therefore, this high potential project bears the abovementioned risk and justifies the endeavours and resources.

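### The therapy comparison in Section 4 (signature-positive versus signature-negative patients on active treatment) is prognostic and cannot by itself support the personalised-therapy conclusion; Sections 4 and 5 need reconciling

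*Protocol article*

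**What the plan says.** Section 4 of the protocol article describes GRAY-ZONE: "A total of 3000 troponin positive patients presenting at ER/ CPU with acute chest pain, but ruled-out ACS", who "will be assigned randomly to Aspirin and/ or Atorvastatin versus placebo (2 × 2 factorial design"). The signature is to be applied retrospectively, first to see whether it predicts ischaemic events over 12 months. For therapy, the section names one comparison: "the clinical event rate in PREMED-CAD-biomarker positive versus PREMED-CAD-biomarker negative patients of the three active, well-tolerated therapies". The parenthesis that follows gives the three as "Aspirin, Atorvastatin, Aspirin combined with Atorvastatin"; placebo is not among them. The section then closes: "This project directly paves the way to personalized and biomarker-guided therapy".

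Section 5 returns to the subject. It says that access to the trial permits "the therapeutic evaluation of the biomarker signature, since the ischemic subjects of the clinical trial will be assigned to four different medication therapies", and it looks ahead, "even towards personalised medicine application using therapy-response analyses". It does not say which groups would be compared. Neither section, nor any other part of the article, states a treatment-versus-placebo effect by signature status or a treatment-by-signature interaction.

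**The concern.** Two questions are being run together. A prognostic question asks whether positives have more events than negatives. A predictive question asks whether treatment changes risk more in positives than in negatives. Only the second can guide the choice of therapy, and it needs an untreated (or otherwise randomised) comparator within each signature group.

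The comparison in Section 4 addresses the first question, among treated patients only, yet it leads into a conclusion about the second. GRAY-ZONE has the randomised placebo data that the second question needs. What is at stake is whether a statement on biomarker-guided therapy would rest on the randomisation or on a contrast between two risk groups.

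**Working it through.** **Inputs from the article.** 3000 patients; a 2 x 2 factorial with placebo; three active therapies named in the Section 4 comparison; four therapies mentioned in Section 5; 12 months of follow-up for events. The article gives no event rate, signature prevalence, allocation ratio, alpha or power for this analysis, so there is no figure of its own to reproduce. All rates below are assumptions.

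**Step 1: what the stated comparison estimates.** Let p1+ and p1− be the event rates on active treatment in positives and negatives, and p0+ and p0− the rates on placebo.

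- Stated comparison: p1+ / p1−.
- Treatment effect by group: RR+ = p1+ / p0+ and RR− = p1− / p0−.
- Differential benefit: RR+ / RR− = (p1+ / p1−) ÷ (p0+ / p0−).

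The stated comparison is only the numerator of the last expression. Without the placebo ratio the differential benefit is not determined.

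**Step 2: numbers.** Hold the active-arm rates at 8% (positive) and 4% (negative), so the stated comparison is always 8/4 = 2.0.

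| Placebo rates, pos / neg | RR+ | RR− | RR+ / RR− | Meaning |
|---|---|---|---|---|
| 8% / 4% | 8/8 = 1.00 | 4/4 = 1.00 | 1.0 | no benefit in either group |
| 10% / 5% | 8/10 = 0.80 | 4/5 = 0.80 | 1.0 | equal relative benefit |
| 12% / 4% | 8/12 = 0.67 | 4/4 = 1.00 | 0.67 | benefit in positives only |
| 8% / 6% | 8/8 = 1.00 | 4/6 = 0.67 | 1.5 | benefit in negatives only |

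One observed ratio fits four different treatment conclusions. The algebra in Step 1 shows that this does not depend on the rates chosen.

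**Step 3: precision of the interaction.** Assume 4% to 10% of 3000 patients have an event (120 to 300 events), half are positive, 1:1 allocation within a factor, two-sided 5% alpha and 80% power (1.96 + 0.84 = 2.80).

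- Events spread equally over the four treatment-by-signature cells: SE of the log ratio of HRs = √(16/events). This is 0.365 at 120 events and 0.231 at 300. Detectable ratio exp(2.80 × SE) = 2.78 and 1.91.
- Events split 2:1 between positives and negatives: the cells hold D/3, D/3, D/6 and D/6 of D events, so the variance is 2 × 3/D + 2 × 6/D = 18/D. SE = 0.387 and 0.245; detectable ratio about 3.0 and 2.0.

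A check on the risk-ratio scale (750 per arm, prevalence 30% to 50%, event rates 5% to 16%) gives an SE of 0.21 to 0.35 and a detectable ratio of about 0.38 to 0.55, which is 1/0.38 = 2.6 to 1/0.55 = 1.8 when inverted. The order of magnitude is the same.

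**The case against.** **Placebo may be intended.** Section 5 counts four therapies. With three active ones, the fourth must be placebo, and it speaks of therapy-response analyses. The sentence in Section 4 is loosely built and may only be naming the drugs under study in a placebo-controlled trial. This stands: a reader might infer that placebo has been deliberately excluded, and the article does not establish that. But Section 5 names no contrast, so it does not correct the one in Section 4.

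**The active arms are not without randomised information.** The combination can be compared with either drug alone, by signature status. A reader might therefore take the point to be that the three active arms can never show differential benefit; that would be too strong. These contrasts are not proposed in the article, however. They would show add-on benefit only, not benefit over no treatment. On the assumptions of the risk-ratio check they would also be less precise (SE 0.30 to 0.49).

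**Nothing says the result would be misread.** One can construct cases in which the active-arm ratio misleads. With an assumed placebo HR of 2.0 and each drug acting only in positives at HR 0.7, the active arms average 2.0 × (0.7 + 0.7 + 0.49)/3 = 1.26, so a signature that picks out responders looks weaker. A reader might infer that the therapy conclusion would be reversed. The article does not say how such a ratio would be interpreted, and Section 4 also plans a separate prognostic assessment, so that inference is not supported.

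**Scope.** This is a consortium article on a retrospective, post-hoc use of the trial. Model form and interaction terms are normally left to fuller documents, and their absence is no fault. What remains is that the comparison the article prints does not support the conclusion it prints.

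**Conclusion.** The point holds in this form: the therapy comparison stated in Section 4 is a non-randomised prognostic contrast under treatment. By itself it cannot show whether signature-positive patients benefit more than negative ones. The step from it to personalised therapy is therefore unsupported as written, and Sections 4 and 5 differ on the therapies involved (three against four).

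That conclusion follows from the definition of the contrast and needs no numerical assumption; the 8% and 4% rates only illustrate it. The precision figures do rest on assumptions (120 to 300 events, half positive). They show that even the right analysis would be exploratory. For a true ratio of HRs of 0.7, power is about 16% with 120 events (0.357/0.365 = 0.98; Φ(0.98 − 1.96) ≈ 0.16) and about 34% with 300 (0.357/0.231 = 1.55; Φ(1.55 − 1.96) ≈ 0.34). The randomisation, primary endpoint and primary analysis of GRAY-ZONE are not affected.

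**What to change.** Reconcile Sections 4 and 5 with a statement to this effect:

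- For each factor of the 2 x 2 design (aspirin versus its placebo; atorvastatin versus its placebo), estimate the randomised treatment effect by baseline signature status in all randomised patients with a usable baseline sample, placebo included.
- Report the treatment-by-signature interaction with its 95% CI.
- Report positive versus negative event rates separately and label them as prognosis only.
- Make the personalised-therapy wording depend on the interaction result, and label that result exploratory.

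The regression model, and whether the score enters as continuous or dichotomised, can be left to the analysis plan.

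The cost is wording and analysis time. The signature is applied retrospectively and the trial already banks baseline samples, so no new patients are needed; samples from placebo patients must be assayed if that was not already planned. The downside is a wide interval for the interaction, and hence a more modest therapeutic claim.

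### The signature/therapy evaluation in GRAY-ZONE is listed as positive-versus-negative event rates within three active cells, which cannot show treatment-effect modification and does not use the 2 × 2 factorial design

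*Protocol article*

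**What the plan says.** All of the relevant text is in the protocol article.

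- **Design (section 4, Translational Aspect—GRAY-ZONE).** The trial has "A total of 3000 troponin positive patients presenting at ER/ CPU with acute chest pain" in whom acute coronary syndrome was ruled out. They "will be assigned randomly to Aspirin and/ or Atorvastatin versus placebo (2 × 2 factorial design").
- **Signature/therapy evaluation (section 4).** The stored samples will allow the consortium to investigate "the clinical event rate in PREMED-CAD-biomarker positive versus PREMED-CAD-biomarker negative" "patients of the three active, well-tolerated therapies (Aspirin, Atorvastatin, Aspirin combined with Atorvastatin"). Placebo is not in this list.
- **Use of the result (section 4).** The section closes: "This project directly paves the way to personalized and biomarker-guided therapy".
- **Use of the result (section 5, Challenges and Risks).** Access to the trial is said to permit a therapeutic evaluation of the signature, because "the ischemic subjects of the clinical trial will be assigned to four different medication therapies". The collaboration is said to have the potential to go "even towards personalised medicine application using therapy-response analyses".

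Section 4 calls the application of the signature in GRAY-ZONE retrospective. Section 5 calls the analyses of its diagnostic value post hoc. The article states no significance level, interaction model or success rule for the therapy evaluation.

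**The concern.** The comparison that is described does not match the question it is meant to inform.

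Biomarker-guided therapy needs evidence that the effect of a drug differs between signature-positive and signature-negative patients. That is an interaction between signature and randomised treatment. Event rates in positive versus negative patients within an actively treated cell show only that the signature predicts risk under that treatment. A purely prognostic signature would give a positive result in every cell, and chance could make it significant in one cell and not in another. A reader could then take a prognostic finding as guidance on whom to treat with what.

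The list of therapies also does not follow the design. A 2 × 2 factorial trial poses two treatment questions, aspirin yes/no and atorvastatin yes/no, and every patient contributes to both. Working cell by cell gives up that advantage in an interaction analysis, where precision is already scarce.

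**Working it through.** The article gives no figure for this evaluation, so there is nothing to reproduce. The check has three parts.

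**Inputs.** From section 4: 3000 patients, 2 × 2 factorial, hence four cells. Assumed, because not stated: equal allocation (3000 / 4 = 750 per cell), 12-month event proportion 3–10%, share of signature-positive patients 20–50%, two-sided 5% level, 80% power.

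**1. What the listed contrast estimates.** Write p₊c and p₋c for the event rates of signature-positive and signature-negative patients in cell c, with c = 0 for placebo.

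- Listed contrast in cell c: R_c = p₊c / p₋c.
- Treatment effect against placebo: p₊c / p₊0 in positives and p₋c / p₋0 in negatives.
- Effect modification: (p₊c / p₊0) / (p₋c / p₋0) = R_c / R_0.

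Suppose the signature doubles risk on placebo, so R_0 = 2. A therapy with no effect gives R_c = 2. A therapy that halves risk in everyone also gives R_c = 2. R_c alone therefore says nothing about modification, and R_0 is not among the listed comparisons. Formally comparing the combination cell with a single-drug cell would give an interaction for the added drug on the background of the other. The article does not state that comparison, and it too would use only two of the four cells.

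**2. How easily the three cells disagree by chance.** Assume no treatment effect, a signature that doubles risk, 30% positive and 5% events overall.

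- Rates: 0.05 / 1.3 = 3.85% in negatives and 7.69% in positives.
- Patients per cell: 225 positive, 525 negative.
- SE of log R_c = √[(1 − 0.0769)/(225 × 0.0769) + (1 − 0.0385)/(525 × 0.0385)] = 0.318.
- Expected z = ln 2 / 0.318 = 2.18, so each cell is significant with probability about 0.59.
- Probability that the three cells do not all agree: 1 − 0.588³ − 0.412³ ≈ 0.73.

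By the same formula, 30–50% positive and 3–10% events give about 0.29 to 0.75. A pattern in which the signature appears to matter on one drug and not on another would be common with no difference in response at all.

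**3. Precision if each cell is compared with placebo.** For rare events, the variance of the log interaction is approximately the sum of 1/events over its four groups. With 30% positive and 5% events in both signature groups:

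| Analysis | Patients per side | Events per side (positive / negative) | Variance | SE |
|---|---|---|---|---|
| One cell versus placebo | 750 | 11.25 / 26.25 | 2 × (1/11.25 + 1/26.25) = 0.254 | 0.504 |
| Factor level | 1500 | 22.5 / 52.5 | 2 × (1/22.5 + 1/52.5) = 0.127 | 0.356 |

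- Variance ratio: 0.254 / 0.127 = 2.0. SE ratio: √2 = 1.41. Neither depends on the assumed event rate or signature share.
- Ratio of hazard ratios detectable at 80% power, exp[(1.96 + 0.84) × SE]: 4.1 by cell and 2.7 at factor level. Over 20–50% positive and 3–10% events: 2.5–8.1 by cell and 1.9–4.4 at factor level.

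The factor of 2 assumes that the other drug does not change the number of events. If it lowers events by a fraction f, the second stratum carries (1 − f) times the information and the variance ratio is 1 + (1 − f) = 2 − f. For f = 0.25 this is 1.75, an SE ratio of 1.32.

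**The case against.** The strongest reply is that the article fixes no model. The parenthesis may only name the active treatments, section 5 refers to all four treatment groups, and nothing says that GRAY-ZONE's own treatment comparison leaves the factorial margins. The work is retrospective and is described as a potential. GRAY-ZONE is also separately funded, and its protocol is not shown.

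Much of this stands. The loss of precision arises only if the evaluation is analysed as listed. It concerns the signature analysis, not the trial's primary comparison. It does not remove the point that the one comparison the text describes is prognostic while the use drawn from it is therapeutic. In section 5 the post-hoc label is attached to the diagnostic value; the therapeutic evaluation follows without an exploratory label.

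A reader might infer something stronger: that three therapies tested without a hierarchy or alpha split yield a false therapy-by-signature claim in more than one trial in ten. The arithmetic is right under its assumptions: three unadjusted two-sided 5% interaction tests give 12.6% if they share a placebo cell and 14.3% if independent. But the article states neither such tests nor a significance level, and at an assumed 1% level the figures are 2.7–3.0%. A condensed article may also leave multiplicity rules to a full protocol or SAP that is not shown. Those percentages are therefore not a property of this plan, and the missing hierarchy is not a finding.

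It is also fair to say that the factor-level estimate averages over the other drug. If the two drugs modify each other's effect, it answers a different question from the single-cell comparison.

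**Conclusion.** The point holds in a limited form. As listed in section 4, the evaluation consists of prognostic contrasts within three active cells and cannot show whether the signature modifies treatment effect, although sections 4 and 5 link it to guided therapy and therapy response. This part follows from the definitions and needs no numerical assumption.

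If each active cell were compared with placebo, each interaction would rest on about 1500 of 3000 patients. Its variance would be about twice that of the factor-level interaction (SE about 1.41 times), given equal arms, no aspirin-atorvastatin interaction and little effect of the other drug on event numbers. The combination-versus-placebo comparison has no direct factor-level counterpart, because it mixes the two drugs. The detectable effects shown above also depend on the assumed event rate, signature share, level and power.

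The documents do not support a claim of inflated error, or a claim that the trial as a whole gives up its factorial analysis.

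**What to change.** In sections 4 and 5, replace the three-therapy comparison with two named interactions in all 3000 randomised patients, placebo included:

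1. signature × aspirin (yes/no), adjusted for atorvastatin;
2. signature × atorvastatin (yes/no), adjusted for aspirin.

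Take signature status from the baseline sample. Report single-cell and combination results, and the three-way term, descriptively. Label the therapy-response evaluation exploratory, and let the statement on biomarker-guided therapy rest on the two interactions. Keep the positive-versus-negative event rates as evidence on prognosis, under that name. Holm adjustment of the pair is optional if the exploratory label is used.

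The cost is wording and a slightly different regression model, with no extra patients, samples or assays. The drawbacks are that a combination-specific response is descriptive only and that the personalised-therapy claim becomes more modest.

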## 5. Challenges and Risks

Because of the complexity of the project including the translational approach, this project has explicit challenges and risks. The project is based on the ‘stratification tool’—the biomarker signature—which allows the identification of subjects at early risk for myocardial infarction. The translational quality of the biomarker signature will be evaluated by the application in the randomized GRAY-ZONE clinical trial. This will allow, by immediate post-hoc analyses, to determine the diagnostic value of the biomarker signature (‘at risk’ = MI within 12 months). Moreover, the exclusive access to this clinical trial allows the therapeutic evaluation of the biomarker signature, since the ischemic subjects of the clinical trial will be assigned to four different medication therapies. This implies that the early stage of biomarker derivation is crucial for all following steps. There is no immediate clinical endpoint in our trial—a weak and insufficient signature will endanger all following steps and the translation into the clinical trial. On the other hand, this collaboration bears the potential to carry a biomarker signature from early development up to ultimate diagnostic application in an ongoing clinical trial, and even towards personalised medicine application using therapy-response analyses. Therefore, this high potential project bears the abovementioned risk and justifies the endeavours and resources.

## 6. Expected Outcome

Given that CVD represents the most important cause of morbidity and mortality, results of the PREMED-CAD consortium have the potential to reduce morbidity and mortality by an early detection and timely therapy of at-risk subjects. Consequently, the results obtained herein will improve and append the knowledge on possible precision medicine approaches for MI patients.

## Figures and Tables

**Figure 1 biomolecules-10-00125-f001:**
[figure not shown]
Schematic presentation of the methodology that will be followed to achieve the optimal biomarker signature in the PREMED-CAD consortium. Target disease population: the subclinical disease stage, immediately (<12 months) before the occurrence of coronary events will be studied. Work-flow of experiments: through bioinformatics tools and validation in murine models and epidemiological cohorts, the biomarker signature for subclinical ischemia in CAD will be identified and validated in the ongoing clinical trial GRAY-ZONE.

